### Data collection

Figure 1 provides an outline of the RCT. At enrollment, the research assistant will collect baseline demographics data and complete the Peds-QL and EQ-5D-YL with the child and/or caregiver via a face to face meeting or phone review, whichever method is preferred by the caregiver. As the EQ-5D-Y questionnaire is designed for completion by children aged 8–15, we will attempt to obtain both child and parent-proxy completed measures for children in this age bracket.

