**Fig. 1 Fig1:**
[figure not shown]
OT = Occupational Therapist; SP = Speech Pathologist; SW = Social Worker; Psych = Psychologist; PedsQL = Pediatric Quality of Life; GP = General Practitioner; ASD = Autism Spectrum Disorder; EQ-5D-Y: EuroQOL Five Dimension Youth Version

At the first allied health or medical specialist appointment, the research assistant or clinician will meet the caregiver in the waiting area and provide them with a cost diary to complete. Cost diaries will be used to record all travel-related costs as well as the number of hours of caregiver time off work required to attend appointments. For subsequent allied health or medical specialist appointments, the research assistant will obtain cost diaries from the caregiver either on the day or up to 48 h post their child’s appointment at the hospital. Collection of completed cost diaries will be from any of the following modalities, whichever is preferred by the caregiver: face to face, phone review, or email.

The Research Assistant will also complete the Peds-QL, EQ-5D-YL, The Autism Family Experience Questionnaire (AFEQ) and Measure of Processes of Care with the child and/or caregiver either on the day or up to 7 days post their child’s last medical specialist appointment at the hospital. Collection of surveys will be either face to face or in a phone review, whichever is preferred by the caregiver.

For phone reviews, a reminder text message will be sent prior to the scheduled review to remind the caregiver of the scheduled date and time. A reminder text message is planned for this trial to allow caregivers the opportunity to reschedule, if a more appropriate time/date is desired. Additionally, a reminder text message is anticipated to assist with retention of participants over the trial period. Similar to previous trials conducted by the research team, a total number of three communication (e.g. text, phone, letter) attempts is allowed at any review time point [20].

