### Statistical analyses

To account for clustering at the hospital level and repeated measures over time, multivariable mixed-effects regression models will be built to estimate the interventional effect of health related quality of life and patient experiences between and within groups. Multivariable mixed-effects regression models were chosen to to minimise bias due to group imbalance and its effects on the internal validity of the study [23]. For each model building process, variables found to be significantly associated with the outcome measure in the univariable analysis at the 10% level will be retained in the final model. As the primary predictor of interest, intervention effect will be forced into the multivariable model. Continuous outcome measures will be analysed using linear regression models. For dichotomous measures, the analysis will be by binary logistic regression, while multinomial logistic regression will be used to analyse nominal measures. Model diagnostics will be conducted on all models to ascertain their appropriateness. Each model will be tested for violations of model assumptions, the existence of influential points and goodness of fit. Tests for all outcomes will be two-tailed, with levels of statistical significance set at 5%. To assess the missingness mechanism, Little’s test for missing completely at random (MCAR) will be used.

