An economic evaluation will take the form of a cost-consequence analysis, where descriptive statistics including means, standard deviations and 95% confidence intervals will be used to summarise differences across all relevant cost and outcome measures between the two models of care. This type of economic evaluation design was chosen to reflect the nature of the intervention where improvements are expected to be seen across a range of health service and patient outcomes (including family out of pocket costs, health system costs, quality of life, patient experience, patient satisfaction, wait times). The cost-consequence analysis framework allows for any changes in these outcomes to be reported clearly and transparently without the restriction of needing to identify a single outcome measure of interest, as is the case with cost-effectiveness analysis. The reader or decision maker is then able to form an opinion about the value of this service change taking account of all relevant costs and outcomes. Specific cost categories to be reported on in the analysis will include allied health and specialist outpatient appointment costs, emergency department presentations, hospital admissions costs and costs of patient (family) travel and time off work to attend appointments. EQ-5D-Y responses will be converted to a utility score using an appropriate published value set. Utility scores will be reported separately for child self-completion and caregiver proxy completion questionnaires. These utility scores will then be used to generate estimates of Quality Adjusted Life Years (QALYs) for each treatment group.

As this study is registered on the ANZCTR and occurring within Metro North Hospital and Health Service, the trial may be randomly audited by an independent study monitor at any time point in the study. Given that this study is unblinded and not comparing rates of mortality or major morbidity, a data monitoring committee will not be set up for the purposes of this specific study.

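### The economic evaluation names only a descriptive comparison for QALYs and does not use the enrolment EQ-5D-Y utility as a covariate, which costs precision and lets chance baseline gaps into the QALY difference

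*Protocol article*

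**What the plan says.** The economic evaluation (Protocol article, Statistical analyses, second part) is a cost-consequence analysis in which "descriptive statistics including means, standard deviations and 95% confidence intervals will be used to summarise differences across all relevant cost and outcome measures". EQ-5D-Y responses become utilities, and "These utility scores will then be used to generate estimates of Quality Adjusted Life Years (QALYs) for each treatment group". On respondents it adds: "Utility scores will be reported separately for child self-completion and caregiver proxy completion questionnaires".

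Utility is measured twice. Under Data collection, at enrolment, "the research assistant will collect baseline demographics data and complete the Peds-QL and EQ-5D-YL with the child and/or caregiver". The only repeat comes "either on the day or up to 7 days post their child’s last medical specialist appointment at the hospital", so the interval between the two measurements differs from child to child.

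The first part of Statistical analyses sets out a different approach for some outcomes: "multivariable mixed-effects regression models will be built to estimate the interventional effect of health related quality of life and patient experiences". These models are said to be chosen to limit bias from imbalance between the groups. Only the intervention is forced in. Other variables enter through univariable screening at the 10% level.

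**The concern.** A difference between arm means with a confidence interval makes no use of where the children started. A QALY built from two measurements contains the baseline value itself, and the follow-up value is usually correlated with it. If one arm happens to enrol with higher utility, it shows a higher QALY total whatever the pathway did. In a trial of this size such gaps are to be expected.

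The QALY result is one of the consequences that the decision maker is asked to weigh, alongside the aim of showing that quality of life is not compromised. An avoidably wide interval, or a difference partly inherited from enrolment, makes that line hard to interpret. The plan already treats group imbalance as a threat when it models quality of life, but it does not carry that protection over to QALYs.

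**Working it through.** The article gives no QALY or utility figure, so there is no planned value to reproduce.

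**Inputs from the article.** Two EQ-5D-Y measurements, U0 at enrolment and U1 after the last specialist appointment (Data collection). 26 children per group with a 10% dropout allowance (Sample size and statistical power). 26 × 2 = 52 in total, against 56 in the Abstract. 26 × 0.9 = 23.4, so about 23 per arm with both measurements.

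**Assumptions, not in the article.** QALY by area under the curve between two points; one horizon T for all children; the same utility SD s at both times, taken as 0.20; correlation rho of 0.4 to 0.8; T = 1 year.

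**Formulas.**
- QALY per child: Q = T(U0 + U1)/2.
- Expected unadjusted QALY difference caused by a baseline gap d: T(1+rho)/2 × d.
- SE unadjusted: T·s·sqrt((1+rho)/2)·sqrt(2/n).
- SE adjusted for U0: T·s·sqrt((1-rho²)/4)·sqrt(2/n).
- Variance ratio: [(1+rho)/2] / [(1-rho²)/4] = 2/(1-rho). T, s and n cancel.

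**Size of a chance baseline gap.** With n = 23, its SE is 0.20 × sqrt(2/23) = 0.059. For s between 0.15 and 0.30, the probability of a gap above 0.05 is 26% to 57%.

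**Results (n = 23 per arm, s = 0.20, T = 1).**

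| rho | Share of gap carried over | QALY shift at a 1-SE gap | SE unadjusted | SE adjusted | Variance ratio |
|---|---|---|---|---|---|
| 0.4 | 0.70 | 0.041 | 0.049 | 0.027 | 3.3 |
| 0.6 | 0.80 | 0.047 | 0.053 | 0.024 | 5.0 |
| 0.8 | 0.90 | 0.053 | 0.056 | 0.018 | 10.0 |

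A simulation of 20,000 trials with these inputs gave SEs of 0.0495 and 0.0272 at rho 0.4, 0.0526 and 0.0240 at 0.6, and 0.0558 and 0.0178 at 0.8. The simulated variance ratios therefore run from (0.0495/0.0272)² = 3.3 to (0.0558/0.0178)² = 9.8, in line with the formula.

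**Other assumptions.** With 26 analysed per arm, s of 0.20 to 0.25 and rho of 0.3 to 0.7, the SE is 0.045 to 0.064 unadjusted and 0.020 to 0.033 adjusted. At T = 0.5 every absolute figure halves and the variance ratio does not change.

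**Bias check.** A further simulation (26 per arm, s = 0.25, rho = 0.5, T = 1) gave an average difference of about zero for both estimators. The SEs were 0.061 and 0.031, and the slopes on the baseline gap were 0.76 and 0.01.

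**The case against.** The strongest reply is that this reads silence as error. The QALY sentence does not say raw or unadjusted, the list of descriptive statistics is introduced as non-exhaustive, and a condensed article may leave QALY construction to an analysis plan that is not shown. The quality-of-life models, which address imbalance, could also cover EQ-5D-Y utility, and the descriptive summary may sit beside them and not replace them.

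Part of this stands. That the QALYs are to be compared unadjusted is an inference from the method named, not a statement in the article. The point survives because the article does name a method of comparison for the economic outcomes, and that method is descriptive. The regression models do not close the gap. They do not mention QALYs, baseline utility is not guaranteed a place in them, and a repeated-measures model of utility does not itself adjust a QALY that already contains the baseline value.

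A reader might also infer that the QALY result is biased, or that a baseline gap passes through in full. Neither follows. Under randomisation the unadjusted difference averages zero when there is no effect, an ordinary 95% CI already allows for chance baseline variation, and the share carried over is T(1+rho)/2.

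Finally, QALYs are not primary. The Discussion names health service use and costs as the primary outcome, the sample size rests on medical appointments, and no cost-per-QALY ratio or threshold is planned. This limits the weight of the point.

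**Conclusion.** The point holds as a matter of efficiency and chance imbalance in a secondary consequence. The described comparison leaves unused a baseline measurement that the trial already collects. For a correlation of 0.4 to 0.8, the unadjusted QALY difference has 3.3 to 10 times the variance of the adjusted one. That ratio depends on the two-point QALY, equal SDs at the two times and a common horizon, but not on the SD, the sample size or the length of that horizon. The absolute QALY figures rest on assumed SDs, correlations and a one-year horizon, and are illustrations only. Because self-report and proxy utilities are reported separately, and self-report is sought only at ages 8 to 15, the self-report set will probably be smaller than the 23 per arm used here and its absolute SEs correspondingly larger.

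**What to change.** In the economic part of Statistical analyses, state that the between-arm QALY difference will be estimated by linear regression of each child's QALY on arm, baseline EQ-5D-Y utility from the same respondent type, and hospital. Report the adjusted difference with its 95% CI as the QALY result and show the descriptive arm means and SDs alongside. Say how this relates to the quality-of-life models in the first part of the section.

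Separately, state the time horizon over which QALYs are computed. Follow-up is tied to the last specialist appointment, so a common horizon needs an explicit assumption about utility beyond the second measurement for children who finish earlier. That assumption should be written down, because QALYs over unequal intervals would also reflect elapsed time.

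The adjustment needs no new data and costs one extra model per respondent type. The horizon is the less trivial part, since it brings in an extrapolation that the two measurements cannot verify.

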### Ethics approval

The Children’s Health Queensland Human Research and Ethics Committee, Queensland, Australia (HREC/21/QCHQ/77040) approved this trial. Enrolled children and their caregivers will be able to withdraw from the study at any time without explanation or penalty from the research team and staff at Caboolture Hospital and The Prince Charles Hospital. Written informed consent will be obtained from a parent or guardian for participants under 16 years old. Any changes to the study protocol will require additional approval from Children’s Health Queensland Human Research and Ethics Committee, Queensland, Australia. In addition, any major changes to the study protocol will also be updated on the ANZCTR accordingly.

### Trial status

This study is planned to commence recruitment in November 2021 and is planned to continue for an estimated period of 12 months. We plan to publish the trial results in relevant peer-review journals at the conclusion of the trial.

## Discussion

This randomised controlled trial will investigate the impacts of an allied health first contact model for the assessment of paediatric ASD on health service use and costs, family out of pocket costs, patient quality of life, patient satisfaction with care and patient waiting times. It is anticipated that the allied health first contact model will result in the reduction of at least one paediatrician appointment on average per child without compromising on patient quality of life and satisfaction, when compared to the traditional medical specialist first contact model.

To our knowledge, this will be the first randomised controlled trial of an allied health first contact model for the assessment of children with ASD internationally. This is a rigorous study design that will minimise the likelihood of bias in our findings. Nonetheless, some limitations exist. The type of families that consent to be involved in a research study may differ from families that choose not to be involved; this may introduce a selection bias that could limit the generalisability of our conclusions. Data collected from families on their out of pocket costs will be obtained at key time points throughout the trial, but may be subject to the effects of recall bias when asking caregivers to record costs occurring in the past. Data collected on health service use and costs, the primary outcome, will be obtained from administrative databases and are therefore expected to be comprehensive and accurate. However, this will be limited to emergency department presentations, hospital admissions, as well as allied health and specialist appointments that are provided by the health service. Data on primary or community-based care and pharmaceutical use will not be captured within this study.

The methodological and practical challenges of measuring and valuing quality of life in paediatric cohorts are well recognised, [24–26] and the evidence base continues to evolve in this field [27]. Additional challenges are present when children have mental disorders that may impact on cognition, literacy or other factors relating to their ability to respond to a questionnaire. Arguments have been made for the merits and limitations of both child-reported and parent proxy-reported completion. In this study, we will adhere to current guidance suggesting that both types should be collected simultaneously where possible [28]. Nevertheless, future studies could consider the incorporation of clinical outcomes (e.g. cognition, speech and language) in conjunction with caregiver-reported outcomes to strengthen the rationale for healthcare professionals to adopt specific service models in the assessment of ASD in children.

The findings from this study are expected to contribute to the evidence base around the costs and consequences of allied health first contact models for the assessment of children with ASD in the Australian setting. If the study hypotheses prove to be correct, this model may free up scarce health care resources while maintaining, or potentially improving, patient and family quality of life and experience of care. These findings may be useful in informing the wider adoption of these models in Australia and internationally, particularly in healthcare settings where medical specialist shortages exist.

## Data Availability

Data sharing is not applicable to this article as no datasets were generated or analysed during the current study.

## Abbreviations

AFEQ: The Autism Family Experience Questionnaire
ANZCTR: Australia and New Zealand Clinical Trials Registry
ASD: Autism Spectrum Disorder
HREC: Human Research Ethics Committee
NHMRC: National Health and Medical Research Council
PedsQL: Pediatric Quality of Life Inventory (PedsQL)
QoL: Quality of life
SEIFA: Socio Economic Index For Area
EQ-5D-Y: EuroQOL Five Dimension Youth Version
